**Wellness intervention**
Session 1 (*La strada verso il recupero*; Recovery and planning for the future): the session introduces the wellness intervention and focuses on the teenager’s global difficulties and worries following an ABI. The psychologist provides psychoeducation on ABI sequelae and encourages the adolescent and their caregivers to describe their personal experience of the injury and related emotions and concerns.Session 2 (*Fare fatica è normale*; Acquired brain injuries: possible consequences): the session describes the cognitive changes that can occur following ABI, for example, difficulties in memory, attention, and executive functioning (EF) and includes video testimonials of adolescents with ABI discussing such difficulties. The psychologist encourages the teens and their caregivers to describe their personal experience of the injury and its consequences. The content is aimed at providing psychoeducation on ABI sequelae specifically related to the area of cognition.Session 3 (*Essere positivi*; Staying positive and handling stress): the session explains how it is important to hire and maintain a positive attitude in everyday life, but this is not specifically related to the problem-solving process, instead to wellness, reducing perceived stress. The psychologist investigates the family’s use of humor in daily life and encourages them to talk about how they feel and how they react when problems occur.Session 4 (*Lavorare con la scuola*; Working with the school): the session aims at providing parents with information regarding their rights as well as the rights of their adolescent in the education system and with materials and ideas to become advocates for their adolescent and to create an optimal learning environment for their adolescent while respecting the school’s ideas.Session 5 (*Prendersi cura di sè*; Taking care of you): the session focuses on the relationship between sleep, nutrition, hydration, exercise, and cognitive and physical functioning following ABI. The psychologist investigates with the adolescent and their caregivers their habits in these areas. The aim is to support health and wellness.Session 6 (*Gestire lo stress*; Managing your stress): the session explains the consequences of feeling stressed on health and suggests some strategies to manage stress. The psychologist investigates how the adolescents usually cope with stress and helps them to learn the strategies to manage stress and to experiment them in daily life. The aim is to support health and wellness.Session 7 (*Il sonno*; Sleep): the session shows the possible sleep changes following ABI and gives advice to improve sleep quality to support health and wellness. The psychologist investigates the adolescent’s sleeping habits and, if necessary, helps them to improve sleep quality. The aim is to support health and wellness.Session 8 (*Dopo la scuola superiore*; After high school): the session offers the adolescent an overview on the opportunities provided by the Italian system in terms of education and work activities after high school, with a primarily psychoeducational focus. The psychologist helps the adolescents to think about what they would like to be when they grow up and what paths they could follow.Session 9 (*Emozioni di chi si prende cura*; For parents: family coping): the session shows the possible emotional difficulties of caregivers of adolescents with ABI and offers strategies for managing stress within the family context. The psychologist reviews with the caregivers their unique responses to the injury, acknowledging that responses are as unique as they are, with a focus on normalizing their emotional reactions.Session 10 (*Parlare con i vostri ragazzi*; Talking with your teenager): the session helps the parents to become good listeners and good communicators to improve their communication with the adolescents and the families to support a calm family environment and overall family wellness. The psychologist engages the parents in role-playing to allow them to improve their communication abilities.

### I-TOPS Intervention (ie, Experimental Intervention Group)

The qualitative data on the process of adaptation of the original TOPS program to the Italian context (ie, I-TOPS) are extensively reported as a case study in a paper published in 2021 [31]. In summary, the adaptation process comprised focus groups with parents of adolescents with TBI to understand the needs of Italian patients and their families; after a literacy translation of the original program into the Italian language, they were asked their opinions on the relevance and clarity of the program content. The main suggestions were related to the scripted videos, with recommendations to emphasizing nonverbal aspects of communication that are integral to the Italian culture. Furthermore, a clearer depiction of the consequences of negative behaviors in the videos was required. The translation of the original TOPS program text from the English language to the Italian language was completed by 3 different psychologists with expertise in the field of brain injury and cognitive behavioral therapy. Translations were subsequently produced by 1 bilingual expert via forward-backward methods, and discrepancies were discussed and resolved. The final text was checked by adolescents with TBI, their parents, physicians, and adolescents of a local school class. Any suggested changes were accepted if they did not alter the meaning of the original sentence. This process required 5 months of work, during which further content revisions were made to improve ease of comprehension and flow in the Italian language.

The regular version of the I-TOPS intervention consists of 10 core sessions focused on problem-solving, EF, behavioral strategies, and social skills and 10 supplemental sessions. Before starting the program, the psychologist will meet with the adolescents and their family to learn about the specific issues occurring in their everyday setting with respect to organization or planning, social interactions, and emotion control that they want to work on during the intervention. Thus, although the I-TOPS program is delivered according to a defined protocol and content, the problem-solving will focus on personalized, everyday issues that the adolescents and their families have identified. The 10 core modules consist of self-guided didactic content regarding the steps of problem-solving and strategies for managing everyday challenges, brief videos modeling these skills, and exercises to support implementation. The adolescents and their families will complete a new module approximately every 15 days. Each web-based session will take 30 to 45 minutes to complete depending on the adolescent’s level of attention. The parent or parents will work with the adolescent to complete each module. The program will not provide any feedback on the activities completed. After the family has completed and reviewed the contents of each session, the trained psychologist will conduct a video meeting of approximately 1 hour with the adolescent and the parent to review the web-based content and practice the problem-solving skills, focusing on a problem identified by the family related to the intervention content from the web-based learning modules (ie, organization or planning, social interactions, and emotion control). Ideally, video meetings should be provided bimonthly, but this period can be slightly adjusted according to family commitments. Completion of all 10 sessions is expected to take each family 5 months. Supplemental sessions will be recommended if their specific content is determined to be potentially beneficial in addressing the ongoing problems of the adolescent or the family identified at the baseline assessment. Therefore, considering supplemental sessions (a maximum of 2 supplemental sessions will be scheduled for each adolescent and family), we anticipate that participants will take approximately 6 months to complete the program.

### Wellness Intervention (ie, Active Control Training)

The active control wellness intervention was developed by translating the original TOPS program contents related to health and wellness into the Italian language, usually included in supplemental sessions, or contents included in original core sessions related to psychoeducation on TBI. In addition, in this case, the translation of the original TOPS program text from the English language to the Italian language was completed by 3 different psychologists having expertise in the field of brain injury and cognitive behavioral therapy. Translations were subsequently produced by 1 bilingual expert via forward-backward methods, and discrepancies were discussed and resolved.

Patients included in the wellness intervention will complete the treatment according to the same schedule as patients of the experimental group but will not receive direct intervention on EF nor support with respect to the problem-solving process. This control treatment focuses on health and wellness but omits contents on problem-solving, EF, behavioral strategies and social skills, and goal setting. The wellness intervention consists of 10 core sessions and 3 supplemental sessions to provide adolescents and their families with a program having the identical structure to the original I-TOPS intervention. The wellness intervention represents an active control training. No feedback will be automatically provided on the activities completed by the program. Bimonthly meetings of a brief duration (ie, about 15 minutes each) with the psychologist will focus on promoting knowledge regarding the consequences of ABI and on healthy lifestyle behaviors to improve wellness and will have the goal to sustain compliance. Completion of all 10 sessions and potentially supplemental ones (a maximum of 2 supplemental sessions will be scheduled for each adolescent and family) is expected to take each family a total of 6 months, similar to the experimental TOPS program. The active control group allows us to control for the placebo effects associated with being involved in a rehabilitation treatment and to isolate the effects of problem-solving training in the I-TOPS intervention.

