## Methods

### Trial Design

We will conduct a single-center, 2-arm, parallel-group RCT. The trial will apply a pre-post design, with a baseline preintervention assessment (T0), a postintervention assessment immediately after the 6-month intervention period (T1), and a long-term follow-up assessment conducted 6 months after the end of the intervention (T2). Participants will be randomly assigned to groups in a 1:1 ratio to receive the I-TOPS or the wellness intervention. The wellness intervention presents the same structure as the I-TOPS intervention but omits contents related to problem-solving. No change to the I-TOPS or wellness intervention content will be made during the trial; therefore, both interventions will be delivered in their initial Italian version. Eventual failures or system downtimes will be recorded and considered for the evaluation of the feasibility of the training, but no changes in functionality will be made. The trial was registered on ClinicalTrials.gov (NCT05169788) on December 23, 2021.

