### Study Setting

The I-TOPS and wellness interventions will be delivered remotely using a web-based platform including web-based learning modules. Participants will complete the intervention in an everyday setting, generally at home using a computer, as the program is not compatible with tablets and mobile phones. Every 2 weeks, a psychologist located in the rehabilitation center (ie, Scientific Institute IRCCS E. Medea in Bosisio Parini, Lecco, Italy) will contact patients and families using the Google Meet videoconference platform to provide remote monitoring, content discussion, and support on the problem-solving process for the I-TOPS intervention and remote monitoring and content discussion only for the wellness intervention.

Demographic, clinical, and outcome data will be collected and stored at the Scientific Institute IRCCS E. Medea.

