### Efficacy Outcomes

A total of 9 outcome measures will be used to test preliminary evidence of training efficacy. Specifically, 7 self-assessed outcome measures (ie, 5 questionnaires for parents and 2 questionnaires for adolescents), 2 performance-based tasks assessing social cognition taken from a standardized neuropsychological battery, and a virtual reality–based assessment of everyday setting EF will be used. Questionnaires will be sent to patients and families in a sealed envelope; after completing them, participants will be required to return them to the research staff using an envelope with a postmark included in the sealed envelope within 2 weeks. The performance-based subtests assessing social cognition and the virtual reality–based assessment will be administered remotely using the Google Meet videoconference platform.

A detailed description of outcome measures is provided in Textbox 4. The sample of this study will include adolescents aged 11 to 19 years, but some measures and questionnaires have been standardized for populations having a lower maximum age range; however, they will be adopted for this study as no other measures with the same characteristics are available in the Italian language. The individual measures affected by this problem are clearly described in Textbox 4.

All outcome measures will be administered at T0 (ie, preintervention assessment), T1 (ie, immediately after the 6-month intervention), and T2 (ie, 6 months after the end of the intervention).

For the questionnaire outcomes, approaches to missing individual items will follow the guidelines for missing item procedures indicated in the manual for each questionnaire. If no guidelines for individual missing items are available, the mean of the completed items will be used to replace missing items if ≤10% are missing.

A summary of outcome measures to test training efficacy is presented in Textbox 5.

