### Strengths and Limitations

The planned study possesses a number of strengths, including the use of an active control group (ie, wellness intervention) instead of a passive one, which allows controlling for placebo effects. Furthermore, although the I-TOPS program involves self-directed, web-based learning modules, the provision of active problem-solving therapy by a trained cognitive behavioral psychologist constitutes a key aspect for the success of this RCT. In support of this, a recent study highlighted the fundamental role of patient-therapist engagement in obtaining good results during the rehabilitation therapy [77]. Finally, the use of the computer, rather than a smartphone, for treatment delivery should allow adolescents to maintain an adequate level of commitment and concentration while performing the I-TOPS intervention, requiring them and their families to carry out the program in a quiet place at home and not in random places (eg, on the beach and means of transportation). However, at the same time, this requirement may restrict treatment access and preclude participation by families who do not have the financial means to buy a computer and the necessary equipment for the videoconferences. Furthermore, families who go on vacation during the 6-month intervention period will have to plan to bring a computer to continue the program or postpone appointments if they are unable to access a computer, which may cause problems with respect to the treatment schedule. At the same time, the long study duration could cause study adherence issues. Nevertheless, it will be the responsibility of our research team to indicate whether the postponement of the sessions is agreed in advance (ie, for holidays or other justified or warranted engagements of the family) or it is instead linked to other factors associated with feasibility issues (eg, forgetfulness, lack of desire or motivation, and failure to carry out tasks). An accurate examination of the feasibility associated with both the training and study design and procedures will be reported.

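### The wellness control cannot isolate problem-solving training, because I-TOPS families are scheduled about four times as much psychologist contact

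*Protocol article*

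**What the plan says.** Trial Design states that the wellness arm "presents the same structure as the I-TOPS intervention but omits contents related to problem-solving". The Wellness Intervention section calls its structure identical to that of I-TOPS. It gives the control two purposes: to account for placebo effects of being in a rehabilitation treatment, and "to isolate the effects of problem-solving training in the I-TOPS intervention". Strengths and Limitations repeats the first purpose, preferring an active control "instead of a passive one, which allows controlling for placebo effects".

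Study Setting gives both arms psychologist contact every 2 weeks. I-TOPS families receive monitoring, content discussion and problem-solving support; wellness families receive "remote monitoring and content discussion only for the wellness intervention". Meeting length also differs:

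- I-TOPS Intervention: after each session "the trained psychologist will conduct a video meeting of approximately 1 hour with the adolescent and the parent", used to go over the web content and to practise problem-solving.
- Wellness Intervention: "Bimonthly meetings of a brief duration (ie, about 15 minutes each) with the psychologist".

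Strengths and Limitations also states that "a recent study highlighted the fundamental role of patient-therapist engagement in obtaining good results during the rehabilitation therapy". The limitations listed there concern computer access, holidays and the length of the study. Unequal contact is not among them.

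**The concern.** To isolate one ingredient, a control has to match the experimental arm on everything else that could plausibly act on the outcomes. Here the arms differ in problem-solving content and also in the amount of time spent with a psychologist. The article itself treats engagement with the therapist as important to good results, so by its own reasoning the second difference is not negligible.

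If I-TOPS does better, the stated inference would credit problem-solving training when some of the benefit might come from more professional attention. This matters most for the seven of nine efficacy measures that are questionnaires, five completed by parents and two by adolescents, because these are the people who received the unequal contact. The two performance-based instruments (JEF-A and the NEPSY-2 subscales), given by blinded testers, are less open to reporting bias but do not separate content from contact either. The question has practical weight: the Conclusions envisage one central therapist supporting many families, and whether the benefit needs the hour of therapist time bears directly on that plan.

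**Working it through.** The article gives no total for contact time, so there is no stated figure to reproduce. Its sample size does reproduce (noncentral F for the group-by-time interaction, f = 0.2, correlation 0.50, alpha 0.05: power 0.803 at N = 42), but this point does not depend on it.

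**Inputs**

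| Input | I-TOPS | Wellness | Source |
|---|---|---|---|
| Psychologist meeting | about 60 min | about 15 min | the two intervention sections |
| Frequency | every 2 weeks | every 2 weeks | Study Setting |
| Core sessions | 10 | 10 | Abstract; the two intervention sections |
| Supplemental sessions scheduled, maximum | 2 | 2 | the two intervention sections |
| Web module | 30 to 45 min | not stated; assumed equal | I-TOPS Intervention |

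**1. Planned psychologist contact = meetings × minutes per meeting**

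- Core sessions: 10 × 60 = 600 min against 10 × 15 = 150 min. Difference 450 min; ratio 600/150 = 4.0.
- With 2 supplemental sessions in each arm, assuming the same meeting lengths: 12 × 60 = 720 against 12 × 15 = 180. Difference 540 min; ratio 4.0.
- Both durations are approximate. If they meant 50 and 20 minutes (an assumption): 500 against 200, ratio 2.5.

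**2. Share of session time spent with the psychologist**

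- I-TOPS: 60/(60 + 45) = 57% to 60/(60 + 30) = 67%.
- Wellness: 15/(15 + 45) = 25% to 15/(15 + 30) = 33%.
- Total scheduled time per session: 105/60 = 1.75 to 90/45 = 2.0 times as long in I-TOPS.

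**3. What the planned model can estimate**

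The Data Analysis Plan has fixed effects for time, treatment and their interaction. Let T = 1 for I-TOPS and 0 for wellness. Planned contact per meeting is then 15 + 45T, an exact linear function of the treatment indicator. A term for planned contact would be collinear with treatment, so the estimated group difference is the effect of content and the effect of contact taken together. Contact actually received varies within arm, but it arises after randomisation and reflects adherence, so adjusting for it would not restore the separation.

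**4. Not counted**

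The I-TOPS section also describes a meeting before the programme to identify the family's own problems. No equivalent is described for wellness and no duration is given. Including it would widen the gap.

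**The case against.** The strongest reply is that the hour is the treatment. The Abstract describes direct training in problem-solving with psychologist support as part of I-TOPS, and the wellness section says openly that this support is withheld. If problem-solving training means training delivered by the psychologist, much of the extra 45 minutes is the ingredient under test. This stands in part: the 450 minutes is not a measure of non-specific attention, and the documents give no way to divide it. It does not rescue the claim of isolation, because the hour also reviews web content, and the additional contact comes bundled with the practice.

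Other points have some force:

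- The two durations are disclosed, and the description of structure sits next to the counts of core and supplemental sessions, for which it is broadly fair. Disclosure does not correct the inference drawn.
- The wellness section limits its placebo claim to the effects of being in a rehabilitation treatment, and an active control does cover more than a passive one. That supports saying placebo effects are partly controlled.
- Participants are to remain blinded and are told nothing about how the arms differ. This limits expectation bias but not a direct effect of more contact.
- The cited work on engagement does not equate engagement with minutes. It shows only that the authors consider the therapist's role important.
- Delivery is finished and cannot be changed. The reporting can be.

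**Conclusion.** The concern holds. The design does not have the isolating property claimed for it: planned psychologist contact differs about 4:1 (about 600 against 150 minutes over the core sessions) and is fully confounded with content. The ratio rests on the stated approximate durations and one meeting per session in each arm; it would still be 2.5:1 under the assumed 50 and 20 minutes. The documents give no effect size for contact time and none is assumed here, so the size of any resulting misattribution is unknown.

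The randomised comparison of the whole I-TOPS package with the wellness programme is unaffected, as are the package-level efficacy objective and the decision on a phase-3 trial. The unsupported part is the attribution to problem-solving training alone and the unqualified statement on placebo control.

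**What to change.** In order of importance:

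1. **Wellness Intervention.** Replace the isolation clause with: *and to compare the whole I-TOPS package, including about 1 hour of psychologist contact per session, with web-based wellness content plus about 15 minutes of contact; the effects of problem-solving content and of contact time cannot be separated.*
2. **Strengths and Limitations.** Say that the control partly accounts for the placebo effects of taking part in a remote rehabilitation programme, and add unequal psychologist contact to the limitations.
3. **Results paper.** Interpret any group difference as a package effect. Report planned contact minutes and meetings held by arm.
4. **Trial Design and Wellness Intervention.** Limit the statements about shared structure to the number of core sessions, platform and schedule. This is minor.

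The cost is a few sentences and one descriptive table row, with no change to data, sample size or model. The price is the narrower claim. Matching meeting length in the control would have removed the confounding at the design stage, at N = 42, but that is no longer possible here; a later trial meant to separate content from contact would need it.
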